#### Sample size justification

2.2.4

Power calculations for the primary cross-sectional study were informed by previous investigations of cortical hyperexcitability and subclinical epileptiform activity (SEA) in neurocognitive disorders [summarized by Horvath et al. (2020)]. Assuming a medium effect size (Cohen’s *d* = 0.5), a two-sided significance level of α = 0.05, and four diagnostic groups, a sample size of 75 participants per group (total *N* = 300) provides more than 90% power to detect clinically meaningful between-group differences in the primary outcomes, including the incidence of SEA and resting-state fMRI hyperactivity.

The mechanistic in-ward substudy is enrichment-based and will include participants demonstrating evidence of cortical hyperexcitability. Assuming a conservative prevalence of approximately 15% across the clinical groups, we anticipate recruiting approximately 45 eligible participants, with an expected final sample of approximately 40 after accounting for an estimated 20% attrition rate.

The mechanistic substudy is designed primarily to characterize within-subject physiological relationships among cortical hyperexcitability, sleep architecture, memory consolidation, and circulating biomarkers using repeated-measures analyses. Because repeated observations substantially increase statistical efficiency for within-subject comparisons, this sample size is considered appropriate for estimating effect sizes, assessing feasibility, and identifying candidate mechanistic pathways. In contrast, more analytically demanding models, including formal mediation analyses and subgroup comparisons across diagnostic categories, are expected to have limited statistical power with the anticipated sample size. Accordingly, these analyses will be considered exploratory and hypothesis-generating, with emphasis placed on effect size estimation, confidence intervals, and model uncertainty rather than statistical significance alone. Findings from these exploratory analyses will inform sample size calculations and analytic strategies for future confirmatory multicenter studies.

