#### Cross-sectional analyses

2.6.1

Data from all diagnostic groups will be pooled into a single multivariate dataset and analyzed using machine learning and dimensional reduction techniques to extract cross-diagnostic patterns of neural and behavioral variance. The model will test for latent factors reflecting shared E/I imbalance across disorders, while *post hoc* analyses identify disorder-specific deviations. Statistical adjustments will account for confounders such as age, medication, and cognitive status.

Primary outcome will be the (Torenvliet et al., 2023) incidence and distribution of SEA, and fMRI hyperactivity in each diagnostic group relative to controls. Secondary outcomes will include relationships between hyperexcitability and (a) structural atrophy and white matter integrity; (b) functional connectivity within and between default mode, salience, and attention networks; (c) CSF and plasma tau/Aβ levels; and (d) domain-specific cognitive performance.

Incidence of hyperexcitability (primary outcome):○Logistic regression models comparing SEA and fMRI-positive status between groups (MCI, ASD, ADHD vs HC), adjusting for age, sex, education, and disease duration where applicable.○Results will be reported as odds ratios with 95% confidence intervals.

Associations with cognition, structure, and connectivity (secondary outcomes):○Within each group, participants will be classified as hyperexcitability-positive vs negative (see section “2.4.1 Participant selection and extraction of normative values”).○For continuous outcomes (neuropsychological scores, cortical thickness/volume, DTI measures, functional connectivity indices, blood-based biomarker concentrations), group comparisons will use *t*-tests or Mann–Whitney U tests depending on normality (Shapiro-Wilk).○For categorical variables, chi-square tests will be used.○Multivariable linear models with covariates (age, sex, education, disease duration, mood/anxiety scores) will assess independent associations.Holm–Bonferroni corrections will be used to control for multiple comparisons.

Cross-modal relationships:○Correlation and regression analyses will examine relationships between spike density and fMRI hyperactivity.○Multimodal latent variable models or clustering approaches will be applied exploratorily to define hyperexcitability phenotypes.

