
It should also be emphasized that the present study is not designed to establish that cortical hyperexcitability plays an identical mechanistic role across MCI, ASD, and ADHD. Instead, the multimodal framework is intended to identify both shared and disorder-specific characteristics of hyperexcitability. Subsequent analyses will therefore examine whether associations between SEA, functional network alterations, structural changes, sleep physiology, and cognitive performance differ between diagnostic groups. These comparisons will help determine whether cortical hyperexcitability represents a common downstream manifestation of distinct disease processes or reflects disorder-specific mechanisms with partially overlapping neurophysiological signatures.

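### The secondary tests specified in 2.6.1 do not estimate whether hyperexcitability associations differ between diagnoses, and they use the data inefficiently for an effect that is common to all three

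*Protocol article*

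**What the plan says.** Section 2.6.1 (Cross-sectional analyses) sets out the secondary associations with cognition, structure, connectivity and blood biomarkers: "Within each group, participants will be classified as hyperexcitability-positive vs negative". Continuous outcomes are compared by t-test or Mann–Whitney test. Multivariable linear models follow, with age, sex, education, disease duration and mood/anxiety scores as covariates. Holm–Bonferroni is applied, and the family of tests is not stated. Neither diagnosis nor a diagnosis-by-hyperexcitability product is among the listed terms, and it is not stated whether these models are pooled or fitted per group.

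The same section opens with a pooled machine-learning and dimension-reduction analysis for shared latent factors. It adds post hoc analyses for disorder-specific departures and names no test for them.

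The closing paragraph of section 3.2 gives the question to be answered. Later analyses will "examine whether associations between SEA, functional network alterations, structural changes, sleep physiology, and cognitive performance differ between diagnostic groups", in order to judge whether hyperexcitability "represents a common downstream manifestation of distinct disease processes or reflects disorder-specific mechanisms".

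**The concern.** Whether an association is shared or disorder-specific is a question about differences between effects. A positive-versus-negative test within MCI, another within ASD and a third within ADHD each ask whether one effect differs from zero. None of them estimates how far the effects differ from each other. One significant and one non-significant result can easily arise from the same true effect, above all when few participants are positive.

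Splitting the data by diagnosis also weakens the evidence for a common effect, because each test uses only a third of the patients. The study could then miss an association that is present in all three disorders, or show it in one or two of them by chance. Both outcomes bear on the transdiagnostic question that the design is built around.

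**Working it through.** **Inputs.** Section 2.2.4 gives "a sample size of 75 participants per group" and "a two-sided significance level of α = 0.05, and four diagnostic groups". Two further inputs are assumptions:
- A standardised difference d = 0.5. The article states it for between-group differences in the primary outcomes. Here it is applied to positive versus negative participants within a diagnosis, with a range of 0.3 to 0.8.
- 15% positive. The article uses this to size the in-ward substudy. Here it is applied to each diagnosis, with a range of 10 to 50%. 0.15 × 75 = 11.25, so about 11 positive and 64 negative.

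Outcomes are taken as independent and normal with equal variance.

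**The plan's own figure.** The article claims "more than 90% power to detect clinically meaningful between-group differences in the primary outcomes". A one-way ANOVA with four groups, N = 300 and f = d/2 = 0.25 has noncentrality 300 × 0.0625 = 18.75 on 3 and 296 degrees of freedom, which gives 96.4% power. The claim is reproduced on that reading. It concerns the primary outcomes; no power is stated for the within-group secondary tests.

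**Power of one within-group test.** The noncentrality is d × √(n₁n₂/(n₁+n₂)) = 0.5 × √(11 × 64/75) = 1.53 on 73 degrees of freedom. At two-sided 0.05, power is p = 0.327.

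**Three tests of an identical true effect, unadjusted.**
- All significant: p³ = 0.035
- None significant: (1 − p)³ = 0.304
- Mixed: 1 − 0.035 − 0.304 = 0.66

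**With Holm over the three diagnoses.** Holm rejects nothing unless the smallest p-value is below 0.05/3. Power at that level is 0.186, so none is significant in (1 − 0.186)³ = 0.54 of studies. Simulating the full step-down procedure gives none 54%, mixed 43%, all three 3%. Among studies with any significant result, 0.43/(0.43 + 0.03), about 94%, are mixed. In larger families, approximated by 0.05/m, none is significant in 77% (m = 12) or 82% (m = 20).

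**Sensitivity: mixed share, unadjusted, identical effect in all three diagnoses.**

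| d | 10% positive | 15% | 20% | 30% | 50% |
|---|---|---|---|---|---|
| 0.3 | 33% | 38% | 44% | 51% | 56% |
| 0.5 | 58% | 66% | 72% | 75% | 74% |
| 0.8 | 74% | 66% | 51% | 33% | 20% |

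The range is about 20 to 75%. At d = 0.3 the remainder is almost all missed effects. At d = 0.8 with 30% or more positive, the most likely result is significance in all three (67% at 30% positive, 80% at 50%).

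**Pooled model at d = 0.5 and 15% positive (simulated).** The common effect has 75% power at an unadjusted 0.05. The 2-df interaction test rejects in about 5% of studies when the effects are identical. If only one diagnosis has d = 0.5 and the others have none, the interaction test has about 18% power (28% at 30% positive).

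**Precision of a difference between two diagnoses.** In standard-deviation units the standard error is √(2 × (1/11 + 1/64)) = 0.46, so the 95% interval is about ±1.96 × 0.46 = ±0.90. For the common effect it is √((1/11 + 1/64)/3) = 0.19, about ±0.37.

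**The case against.** The strongest reply is that the comparison is already planned. Section 3.2 commits to examining whether associations differ, section 2.6.1 pools all groups for shared factors, and the form of the model could be left to an analysis plan. The within-group tests can also be read as serving Hypotheses 2 to 4, which ask only whether an association exists. This stands in part: the aim is present, and what is missing is a method matched to it. It does not remove the point. The article does specify its secondary tests; those tests cannot answer the section 3.2 question, and they are also the less efficient way to test Hypotheses 2 to 4 for an effect common to the disorders.

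A reader might infer that the study will call an effect disorder-specific whenever the within-group tests disagree. The article does not say so, and sections 3.2 and 3.5 caution against over-reading mechanism. Nor does it say that the adjusted models are run separately by diagnosis.

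A reader might also infer that a shared effect will usually look disorder-specific. That does not hold either. With the planned Holm correction, the most likely result at the central inputs is no significant finding in any diagnosis. With large effects and many positives, all three tests usually succeed.

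The exploratory label in section 2.2.4 does not settle the matter, because it is attached to the in-ward substudy and not to these cross-sectional analyses.

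**Conclusion.** The point holds in a limited form. The specified secondary tests do not estimate differences between diagnoses and are inefficient for a common effect. At d = 0.5 and 15% positive, an effect identical in MCI, ASD and ADHD is significant in all three in about 3% of studies, with or without Holm over three tests. Otherwise it is patchy (66% unadjusted, 43% under Holm) or missed altogether (30% and 54%).

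These figures rest on two borrowed inputs and on equal prevalence and equal effects across the diagnoses. The structural point, that separate tests do not estimate a difference, rests on none of them. The change is worth making before results are seen; it does not threaten the primary analysis.

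**What to change.** For each secondary outcome, fit one linear model across the three patient groups with diagnosis, hyperexcitability status, their interaction and the covariates already listed, using robust standard errors. Then:
- Report the common effect with its confidence interval.
- Report the differences between diagnosis-specific effects with confidence intervals, and base any disorder-specific statement on these and not on which within-group tests are significant.
- Keep the within-group comparisons as descriptive estimates.
- State which tests form the Holm family.
- State that power for heterogeneity is low (about 18 to 28% if only one diagnosis has d = 0.5), so that a non-significant interaction is not read as proof of a shared effect.

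The cost is analysis wording only, with no new participants or measurements. The real price is fewer disorder-specific claims, since the intervals for differences will be wide. The pooled model also assumes common covariate slopes across diagnoses. For age this should be checked, because MCI participants are at least 55 while the ASD and ADHD groups are open to adults generally.

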**Association with cognitive performance.**
*Hypothesis 2:* Higher levels of cortical hyperexcitability are associated with poorer performance across standard neuropsychological measures of memory, attention, executive function, and visuospatial skills.

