All recordings will be independently reviewed by two experienced clinical neurophysiologists who are blinded to diagnosis and other clinical information. Epileptiform discharges will be accepted only when both reviewers reach consensus. Prior to consensus adjudication, inter-rater agreement will be quantified using Cohen’s κ coefficient for the presence or absence of subclinical epileptiform activity, with κ values and 95% confidence intervals reported in the final study results. Discordant cases will be reviewed jointly to establish the final classification. Automated spike detection (Persyst) will serve as a supporting tool for quantifying spike density, amplitude, and duration, while all final classifications remain based on expert visual assessment. The average spike density (spikes/hour) will be computed, and scalp distribution will be categorized (frontal, temporal, parietal, occipital, etc.) using Micromed SystemPLUS 98. Participants will be labeled as EEG-positive or negative for SEA relative to HC normative values obtained from our reference database (ACOL). The SEA detection pipeline is reported in our previous publications (Horváth et al., 2018b; Horvath et al., 2021).

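### Section 2.6.1 tests the secondary associations by positive/negative splits within groups of 75 (about 33% power for d = 0.5), although H2 and H6 are worded as gradients and continuous measures exist

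*Protocol article*

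**What the plan says.** - **Hypotheses (section 1.2).** H2 is graded: "Higher levels of cortical hyperexcitability are associated with poorer performance across standard neuropsychological measures". H6 is also graded and is confined to MCI. H3 and H4 speak of an association without stating a gradient.
- **Measures.** Section 2.3.4 provides a continuous EEG measure: "The average spike density (spikes/hour) will be computed". Section 2.4.1 expresses fMRI metrics as z-scores against the reference database.
- **Analysis (section 2.6.1).** For cognition, structure, connectivity and blood biomarkers: "Within each group, participants will be classified as hyperexcitability-positive vs negative". Positivity is defined in section 2.4.1 as EEG or fMRI evidence. Continuous outcomes are compared by t-test or Mann–Whitney, chosen by a normality test. Multivariable linear models follow, without saying in what form hyperexcitability enters them. Holm–Bonferroni is applied to a family whose size is not given.
- **Power (section 2.2.4).** "a sample size of 75 participants per group (total *N* = 300) provides more than 90% power" refers to the primary outcomes, at d = 0.5 and "a two-sided significance level of α = 0.05". The only prevalence given is in the substudy paragraph: "Assuming a conservative prevalence of approximately 15% across the clinical groups". No power is given for the secondary comparisons.

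**The concern.** Two choices weaken the secondary tests. Splitting within each diagnostic group leaves a small positive arm inside a sample of 75. Reducing density and z-scores to yes/no also removes the gradient that H2 and H6 are about, and the either-modality rule puts people with very different degrees of abnormality in one category.

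The limited-power warning in section 2.2.4 concerns mediation and subgroup models in the in-ward substudy. The cross-sectional secondary hypotheses carry no such warning. A null result there could be read as evidence against a link between hyperexcitability and cognition, structure or biomarkers when the test had little chance of finding one.

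**Working it through.** **Inputs.** From section 2.2.4: 75 per group, d = 0.5, two-sided alpha 0.05, prevalence about 15%. The plan gives d = 0.5 for the primary outcomes, so using it for positive versus negative is an assumption.

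**The plan's own figure.** A four-group one-way ANOVA with N = 300 and f = d/2 = 0.25 has 96.4% power, consistent with the stated figure of more than 90%. A single two-sided 75 vs 75 comparison at d = 0.5 has 86.0%. Neither describes the secondary split.

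**Size of the split.** 0.15 × 75 = 11.25, so about 11 vs 64.

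**Power within a group.** The noncentrality is d / √(1/n₁ + 1/n₂), with n₁ + n₂ − 2 degrees of freedom.
- √(1/11 + 1/64) = 0.326, and 0.5 / 0.326 = 1.53.
- Power is 32.7% by the noncentral t (33.4% by the normal approximation).
- Averaged over Binomial(75, 0.15), where 95% of draws give 6 to 18 positives, it is 32.8%.
- The effect detectable with 80% power is d = 0.93.

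**Range over prevalence (n = 75, d = 0.5, noncentral t).**

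| Positives vs negatives | Power |
|---|---|
| 4 vs 71 | 16% |
| 8 vs 67 | 26% |
| 11 vs 64 | 33% |
| 15 vs 60 | 40% |
| 23 vs 52 | 50% |
| 37 vs 38 | 57% (maximum) |

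These figures are before Holm. If the family held 6 tests (an assumption), the first step at 0.05/6 would leave about 13% for 11 vs 64.

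**Pooled over groups.**
- 15% of the 225 patients is 34. For 34 vs 191, √(1/34 + 1/191) = 0.186, the noncentrality is 2.69 and power is 76%.
- 15% of all 300 is 45. For 45 vs 255, the values are 0.162, 3.09 and 87%.
- If controls had only about 4 positives (5% of 75 = 3.75, an assumption based on the EEG 95th-percentile limit alone), 3 × 11 + 4 = 37. For 37 vs 263, power is 81%.

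**Effect of grading the exposure (n = 75, simulated, scaled to d = 0.5 between positives and negatives).** The documents do not give the distribution of the exposure, so these are illustrations.

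| Assumed exposure and effect | Graded | Split |
|---|---|---|
| Normal measure cut at top 15%, graded effect (r = 0.27) | about 65% | about 33% |
| Skewed or zero-inflated density, graded effect | about 42–51% | about 33% |
| 85% zeros, effect purely present/absent | about 21–26% | about 33% |

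The gain from pooling does not depend on this distribution. The gain from grading does.

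**The case against.** **The gradient is not wholly discarded.** Spike density stays continuous in the cross-modal analysis and in the in-ward mixed models. That stands, but the in-ward models address within-person variation in a selected subset, not H2 or H6 across participants.

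**The linear models may already be graded or pooled.** Section 2.6.1 opens with a pooled dataset and does not state the form of the exposure, and a condensed article may leave this to a fuller plan. The models therefore cannot be counted as dichotomised. What the article does fix is the within-group split for the two-sample tests, and the finding rests on that.

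**The prevalence is called conservative and comes from the substudy paragraph.** True, but it rests on the same definition of positivity, and the 57% ceiling holds at any prevalence.

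**Graded exposure may not help.** This is the strongest objection. If most participants have no spikes and only presence matters, a graded model loses power. That is a reason to keep the binary contrast as a sensitivity analysis.

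A reader might also object to the normality pre-test, or to having both unadjusted and adjusted results. Unadjusted comparison followed by an adjusted model is routine, and these points add little.

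**Conclusion.** The concern holds in this form: the within-group positive/negative comparisons are poorly powered for a medium effect, and for H2 and H6 they do not match the graded wording. The size is about 33% power per test at 11 vs 64, at most about 57% at any prevalence, before Holm; pooling gives about 76% to 87%. This rests on carrying d = 0.5 over from the primary outcomes and on the 15% prevalence.

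Three stronger readings are not supported:
- **That H2, H3 and H6 would very likely come out null.** The figures are single-test power at an assumed effect; no probability for a whole hypothesis follows from them.
- **That all secondary hypotheses are mismatched to their tests.** Only H2 and H6 are worded as gradients. For H3 and H4 the issue is power.
- **That grading the exposure roughly doubles power.** That needs a normally distributed measure and a graded effect.

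The pooled figures cannot be credited to H6. It is confined to MCI, and its CSF part to participants with a clinically indicated lumbar puncture, so it stays limited to 75 people or fewer.

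**What to change.** 1. **H2 to H4:** make the multivariable linear model the confirmatory test for each outcome, fitted in all participants with diagnostic group, age, sex and education.
2. **Exposure:** use log(1 + spike density). In a separate model, use one fMRI deviation z-score named in advance, only for outcomes not derived from fMRI. The connectivity outcomes of H4 therefore use the EEG exposure.
3. **Disorder-specific effects:** add a group × exposure interaction.
4. **H6:** fit the graded model within MCI only and state its limited power.
5. **Multiplicity:** apply Holm to these models.
6. **Positive/negative comparisons:** keep them as descriptive or sensitivity results, to cover a present/absent effect.

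No new data are needed. The cost is more than wording, because section 2.4.1 lists several fMRI metrics and no single deviation score, so one must be chosen before analysis. Results would be expressed per unit of exposure, and power is lost if the true effect is purely present/absent.

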To generate normative EEG values, we perform meticulous EEG preprocessing on 24-h recordings—artifact removal (e.g., eye blinks, muscle noise), filtering, and referencing—to ensure clean data. Two manual expert reviews of the files to identify potential SEA in line with the previously published protocols (Kamondi et al., 2024; Port et al., 2019). To define normal limits, the density, amplitude, duration, and spatial distribution of these events can be quantified across all control recordings. Statistically, normal values are represented by upper tolerance limits (the 95th percentile) of spike density (events per hour) computed from the control group. Normative modeling is applied to further refine these thresholds by accounting for age, sex, sleep state, and recording montage, variables known to influence EEG background and transient patterns. Additionally, spectral power and band ratios (delta, theta, alpha, beta, gamma) are used to construct normative baselines, against which epileptiform spikes produce transient deviations.

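### The Shapiro-Wilk choice between t-test and Mann-Whitney gives no protection against unequal spread in secondary comparisons of roughly 11 against 64 participants

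*Protocol article*

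**What the plan says.** Protocol article, section 2.6.1 (Cross-sectional analyses), secondary outcomes: "Within each group, participants will be classified as hyperexcitability-positive vs negative". Continuous outcomes are neuropsychological scores, cortical thickness and volume, DTI measures, connectivity indices and blood biomarker concentrations. They are compared by t-tests or "Mann–Whitney U tests depending on normality (Shapiro-Wilk"). The section does not say whether the t-test is Student's or Welch's, and it does not mention unequal variances. It also plans multivariable linear models with covariates, without robust variance, and a Holm-Bonferroni correction.

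The subgroup sizes are not stated there but follow from other sections:

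- Section 2.2.4 plans "a sample size of 75 participants per group" and sizes the in-ward substudy by "Assuming a conservative prevalence of approximately 15% across the clinical groups".
- Section 2.4.1 sets the EEG limit in reference controls by "upper tolerance limits (the 95th percentile) of spike density".

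**The concern.** When one subgroup is about six times the size of the other, the pooled variance of Student's t is dominated by the larger subgroup. If the smaller one has a different SD, the standard error of the difference is wrong, and more data of the same proportions would not correct it. Mann-Whitney is also sensitive to unequal spread. A normality pre-test addresses neither, so the stated rule offers no safeguard where this design most needs one.

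The rule covers cognition, cortical structure, DTI, connectivity and plasma markers, and so bears on Hypotheses 2, 3, 4 and part of 6. Holm-Bonferroni assumes that each p-value is valid and cannot repair p-values that are individually too small.

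**Working it through.** **The plan's own figures.** The plan gives no error rate or power for these comparisons. Its statement of more than 90% power (d = 0.5, two-sided 0.05) concerns differences between diagnoses. A four-group ANOVA with N = 300 and f = d/2 = 0.25 meets it (96.4%), while a two-sided comparison of two groups of 75 gives about 86%. It does not bear on the positive-versus-negative tests. The 15% does: 0.15 × 300 = 45 reproduces the substudy figure in section 2.2.4.

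**Subgroup sizes.** 0.15 × 75 = 11.25, so about 11 positive and 64 negative. For controls on the EEG criterion alone, 0.05 × 75 = 3.75, so about 4 against 71.

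**Student's t by formula.** Let r be the SD of the positive group divided by that of the negative group, with the negative SD set to 1.

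- True variance of the difference: r²/11 + 1/64.
- Variance the test uses, on average: [(10r² + 63)/73] × (1/11 + 1/64).
- k is the square root of true over used. The error is about 2Φ(−1.993/k), where 1.993 is the 5% critical value on 73 degrees of freedom.

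At r = 2: true 4/11 + 1/64 = 0.379; used (103/73) × 0.1065 = 0.150; k = 1.59; error about 21%.

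At r = 1.5: true 0.220; used 0.125; k = 1.33; error about 13%.

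At r = 0.5: true 0.038; used 0.096; k = 0.63; error about 0.2%.

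**Simulation of the full rule.** Normal data, equal means, 11 against 64, 10,000 runs per row. I assumed that Shapiro-Wilk is applied at 5% in each subgroup, with the t-test used if both pass and Mann-Whitney otherwise. Error in % at nominal 5%:

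| r | Student, no pre-test | Rule with Student | Mann-Whitney alone | Welch alone | Rule with Welch |
|---|---|---|---|---|---|
| 0.5 | 0.3 | 0.3 | 0.9 | 4.9 | 4.5 |
| 0.67 | 1.1 | 1.3 | 2.4 | 5.5 | 5.2 |
| 1 | 4.9 | 5.0 | 4.7 | 5.1 | 5.2 |
| 1.25 | 9.1 | 9.0 | 6.8 | 5.1 | 5.6 |
| 1.5 | 13.4 | 13.2 | 8.2 | 4.9 | 5.5 |
| 2 | 21.7 | 21.3 | 12.0 | 5.1 | 6.3 |

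Repeat simulations put the rule with Student's t at 9 to 10%, 13 to 14% and 20 to 22% for r = 1.25, 1.5 and 2. Columns two and three agree within simulation error: for normal data the pre-test neither causes nor removes the inflation.

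**Other splits (rule with Student's t, normal data).**

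- 4 against 71: 10.7%, 16.7% and 26.9% at r = 1.25, 1.5 and 2.
- 23 against 52 (30% positive): about 7%, 9% and 12 to 13%.
- 37 against 38: 5.0% to 5.4% at every ratio from 0.5 to 2.

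**Skewed data.** Lognormal with log-SD 0.5, shifted to equal means, 11 against 64. Both subgroups pass Shapiro-Wilk in only about 2% of runs, so Mann-Whitney is nearly always used. As a test of means the rule then errs in about 11 to 12% at r = 1.5 and 16 to 18% at r = 2, whichever t-test was intended. Welch alone gives 7 to 8%.

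**The planned linear model.** With four noise covariates, 11 against 64 and normal data, ordinary standard errors give about 12 to 13% at r = 1.5 and 19 to 21% at r = 2. HC3 standard errors give about 5 to 6%.

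**The case against.** The strongest reply is that the larger figures depend on choices the article does not make. It does not name Student's t, and a condensed article may leave that to an analysis plan not shown here. With Welch the rule is close to nominal for normal data. This stands, and the absence of the name is not itself the fault. It does not rescue the rule for skewed outcomes, where the stated pre-test selects Mann-Whitney.

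Nor do the documents give SDs, so both the size and the direction of unequal spread are assumed. The 11 against 64 split is derived from a prevalence that the protocol calls conservative. Positivity by either EEG or fMRI could be more common, and near an even split the problem disappears. All of this stands.

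A reader might infer four stronger things that the documents do not support:

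- **False positives always rise when spread differs.** They do not. If the positive group is the less variable, normal data give a test that is too conservative and loses power.
- **The pre-test produces the inflation.** For normal data it does not; it merely fails to protect.
- **Mixing mean and rank tests invalidates Holm.** It does not. Holm accepts any set of valid p-values, and the article defines no family.
- **The unadjusted comparisons are superfluous.** They are ordinary descriptive reporting, and the linear models have their own stated role.

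Finally, Mann-Whitney rejections with skewed data of unequal spread are errors only as statements about means; the distributions do differ.

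**Conclusion.** The point holds in limited form. The stated rule is miscalibrated if positive and negative participants differ in spread, because the pre-test looks at shape and the protocol's own figures imply very unequal subgroups. On normal data with Student's t at 11 against 64, the error runs from below 0.5% at an SD ratio of 0.5 to about 21% at a ratio of 2, and it is 5% at equal SDs. With Welch's t it is about 6% at ratios above 1 for normal data, but the skewed case remains at about 11 to 12% and 16 to 18% for ratios 1.5 and 2.

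These figures rest on an assumed SD range of 0.5 to 2, on the 15% prevalence, and on Shapiro-Wilk being run per subgroup. They do not show that the study's secondary results will carry a 20% error rate. The primary outcome, analysed by logistic regression, is unaffected. The point is minor and worth acting on because the repair costs almost nothing.

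**What to change.** In section 2.6.1:

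- Delete the Shapiro-Wilk pre-test.
- Make the already planned covariate-adjusted linear model the inferential analysis of each continuous secondary outcome, with HC3 or Welch-type standard errors. Promoting the model without robust errors would not help.
- State in advance which skewed biomarkers are log-transformed.
- Apply Holm-Bonferroni to the p-values from these models.
- Keep unadjusted positive-versus-negative comparisons as descriptive, using Welch's t-test if a test is shown.

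The cost is analysis wording only; no further data are needed. Intervals will be slightly wider if variances are in fact equal, and log-transformed biomarkers will be reported as ratios of geometric means instead of differences in means.
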